### Participant timeline

The Standard Protocol Items: Recommendations for Interventional Trials (SPIRIT) table in Fig. 2 shows details on the schedule of enrollment, interventions, and assessments.

**Fig. 2 Fig2:**
[figure not shown]
Standard Protocol Items: Recommendations for Interventional Trials (SPIRIT) *diagram* of enrolment, treatment, and assessments over time

### Measurements

The primary outcome of the trial will be the MOS 36-item Short Form Health Survey mental component summary scale (SF-36 MCS). The secondary outcomes are other sub-items of the MOS 36-item Short Form Health Survey physical component summary scale (other sub items of SF36) [20, 21], PROMIS, physical fitness, and social cognitive theory. Measurements will be conducted in the same place and by the same tester for both the study group and control group strictly adhering to the precautions and operational rules, to ensure that the measurements are scientific and precise.

### Quality of life (QOL)

The MOS 36-item Short Form Health Survey (SF-36)SF-36 is a reliable and manageable questionnaire of QOL, which has been extensively applied in the assessment of the health conditions of patients with chronic diseases. SF-36 includes eight dimensions and two summary tables; the score of each dimension is in the range of 1–100 (100 represents the best health condition).The Patient Reported Outcome Measurement Information System [22] (PROMIS) will be used in the evaluation of physical function, anxiety, and depression of the individuals mainly, including physical functions (such as: can you run or do shopping?), anxieties during the past seven days (such as: I feel fearful), frustrating (such as: I feel useless), sleeping disorders (such as: I have trouble falling asleep), and pain disruptions (does pain limit your housekeeping activities?). The options are categorized into five levels from not at all/no/very weak as the first option to always/very much/very good as the fifth option. It has been demonstrated that PROMIS can be applied in the evaluation of the population of clinic patients [23].

### Physical fitness

Maximal oxygen uptake: this is determined by an improved Bruce plank test [24] which will be strictly adhered to; the heart rate will be monitored by a Polar watch during the test.Stand-up and sit-down chair test (number of times standing up from the chair within 30 s): these outcomes will be used to evaluate leg strength and endurance of the individual. Test procedure: (i) put an upright chair (or a folding chair) against the wall (for the sake of safety); (ii) the individual sits in the middle of the chair with the right left feet apart, equal to the shoulders (one foot may be placed slightly in front of the other) and both arms are crossed around the waist and close to the chest; (iii) during the test, the individual should stand up completely and then sit down completely; (iv) the number of times that the individual stands up from and sits down in the chair within 30 s is recorded; (v) for safety purposes, or when necessary, the individual may use her arms for assistance.Number of arm raises (30 s with a dumbbell of 5 lbs or 2.3 kg): this outcome is used to evaluate the strength and endurance of the upper extremities. Test procedure: (i) a 2.3 kg (5 lbs) dumbbell is used; (ii) put an upright chair (or a folding chair) against the wall (for the sake of safety); (iii) the individual sits close to the side of chair if she has a stronger arm on that side; (iv) the stronger arm holds the dumbbell with the arm naturally hanging straight down over one side of the chair while the body takes a push-up position; (v) the non-moving arm is fixed close to the body so that only the moving arm is moving; (vi) bend and lift the arm to its maximum extent when gradually rotating to the outward position with the palm facing up; (vii) the arm returns to the push-up position and is placed on one side of the chair; (viii) the number of times that the arm bends and lifts is recorded; (ix) precautions include making sure the arm is completely bent and the elbow is completely straightened—it is very important that the upper extremities are stable without swaying.Percentage of body fat [24]: measuring the (i) upper arm (triceps)—vertical direction of skin folds; both arms fall naturally on both sides of the body, measure at the midpoint of the straight line connecting the acromion and the olecranon of the posterior upper arm; (ii) anterior superior iliac spine—oblique direction of the skin folds; measure at the axillary line above the anterior superior iliac spine and follow the natural wing of the ilium; (iii) abdominal skin folds—vertical direction of the skin folds, at 2 cm from the right side of umbilicus. Measure the thickness of the skin folds at these three points, calculate the body density with the three-point method according to the female skin fold measurement and calculation formula, and then calculate the individual’s percentage of body fat.Height, body weight, and flexibility tests.

### Social cognitive indicator

The participant’s social cognitive belief will be evaluated by standard self-report questionnaire [25] including: sport exercises: social support questionnaire; sport exercises: obstruction questionnaire; sport exercises: expected outcome questionnaire; sport exercises: self-efficiency questionnaire. For example: sport exercises: social support questionnaire is to survey whether your family and friends have completed the following items during the past 30 days, including five social support questions (encourage you to exercise, discuss the disadvantages of not exercising, remind you to exercise, share some methods of exercise with you, do exercises together with you). The options include “almost none,” “once,” “sometimes,” “often,” and “always” in sequence. These questionnaires have been subject to normal distribution validation and content validity analysis in previous literature.

### Sample size

A total of 52 participants (26 in each group) completing follow-up will provide 90% power (α = 0.05) to detect 9.5 points [26] in SF-36 MCS assuming a standard deviation of 11.6 points [27]. Assuming a 15% drop-out rate between baseline and follow-up, 60 participants will be enrolled in the study.

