### Statistical analyses

The study results will undergo statistical analysis with SPSS software version 19.0. Comparisons between groups will be an analysis of covariance (ANCOVA) with treatment and baseline entered in the model. Estimate, 95% confidence intervals (CIs), and *p* values will be reported. The analysis population will adopt Intent to treat (ITT) and ignoring missing data.

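### The stated 90% power does not follow from the stated inputs: 26 completers per group give about 82.5% with a two-sided 5% test

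*Protocol article*

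**What the plan says.** The Sample size section of the protocol article gives the whole calculation in one sentence: "A total of 52 participants (26 in each group) completing follow-up will provide 90% power (α = 0.05) to detect 9.5 points" on the SF-36 mental component summary (MCS), "assuming a standard deviation of 11.6 points [27". A second sentence allows for 15% drop-out and sets enrolment at 60. Allocation is 1:1 (Blinding section), and the MCS is the primary outcome (Measurements section).

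The sentence does not say whether α is one-sided or two-sided, which test was assumed, or whether any baseline correlation entered the calculation. Under Statistical analyses the group comparison is an ANCOVA on treatment and baseline, reported as "Estimate, 95% confidence intervals (CIs), and" p values. No one-sided hypothesis appears anywhere in the article.

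**The concern.** A difference, a standard deviation, α, the allocation ratio and a group size fix the power of a comparison of two means, so the claim can be checked in full. A standardised difference of about 0.82 with 26 per group looks too small for 90% power at the usual two-sided 5% level, and 26 is close to what a one-sided formula returns.

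The figure describes the sensitivity of the trial's single primary comparison. If the true power is nearer 80% than 90%, a non-significant result is weaker evidence against a 9.5-point effect than the protocol tells its readers. There is little slack. Sixty enrolled with 15% drop-out leaves 60 × 0.85 = 51 completers. Missing data are to be ignored in the analysis, and the Data collection and management section says there are no plans to promote retention.

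**Working it through.** **Inputs (protocol article).** Difference δ = 9.5, SD σ = 11.6, α = 0.05, target power 90%, 26 completers per group (all Sample size); 1:1 allocation (Blinding).

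Standardised difference: d = 9.5 / 11.6 = 0.819, so d² = 0.671.

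**Which reading gives 26 per group?** Normal approximation, n per group = 2(z_α + z_β)² / d²:

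- One-sided 5%: 2 × (1.645 + 1.2816)² / 0.671 = 25.5, rounded up to 26. This is the stated number.
- Two-sided 5%: 2 × (1.960 + 1.2816)² / 0.671 = 31.3, rounded up to 32.

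With the noncentral t distribution, the smallest group sizes reaching 90% are 27 (one-sided) and 33 (two-sided).

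**Power at 26 per group.** The standard error of the difference is 11.6 × √(2/26) = 3.217, so δ/SE = 9.5 / 3.217 = 2.953.

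| Test | Normal approximation | Noncentral t (50 df) |
|---|---|---|
| One-sided 5% | Φ(2.953 − 1.645) = 90.5% | 89.8% |
| Two-sided 5% | Φ(2.953 − 1.960) = 84.0% | 82.5% |

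The type II error on the two-sided reading is 100 − 82.5 = 17.5%. With the 51 completers that the drop-out assumption leaves (25 and 26), two-sided power is 81.8%.

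**Difference detectable with 90% power, two-sided, 26 per group.** Normal approximation: 3.217 × (1.960 + 1.2816) = 10.4 points. Noncentral t: 10.6 points.

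**Sensitivity to the planned ANCOVA.** Adjusting for baseline multiplies the residual variance by (1 − r²), where r is the correlation between baseline and follow-up MCS. The protocol gives no r, so the values below are assumptions. They also take 11.6 to be the unadjusted SD. Two-sided 5%, 26 per group, noncentral t with one degree of freedom spent on the covariate:

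| Assumed r | Power |
|---|---|
| 0 | 82.5% |
| 0.3 | 85.9% |
| 0.4 | 88.5% |
| 0.45 | 90.0% |
| 0.5 | 91.7% |
| 0.6 | 95.1% |

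**The case against.** The strongest reply is that 82.5% belongs to a t-test that the trial will not run. The planned analysis is ANCOVA, and for any non-zero r of practical size its power is higher. If r is about 0.45 or more and 11.6 is the unadjusted SD, 90% is met. This stands as a statement about the trial's actual power, which is unknown from the document. The 17.5% type II error is what the stated inputs imply, not a forecast for the adjusted analysis. It does not rescue the claim: the sentence rests the 90% on a difference and an SD alone, with no correlation and no hint that the SD is a residual one.

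It can also be said that how 26 was reached is an inference. That is right. The one-sided match holds exactly only for the normal approximation (the t distribution gives 89.8%, so 27 would be needed), and a two-sided ANCOVA with a suitable r would also support 26. The inference is not needed for the conclusion, since the printed power disagrees with the printed inputs under the two-sided 5% level to which the planned 95% intervals correspond.

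The text is a condensed article, so silence on sidedness or correlation is not held against it as an omission. The point is that a figure it does print is not supported by the numbers beside it.

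Finally, about 82% still exceeds the conventional 80%, and readers should judge a null result from the confidence interval. Both are fair: the trial is not shown to be inadequate. The stated figure is still wrong as written.

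**Conclusion.** The concern holds. With a 9.5-point difference, SD 11.6 and 26 completers per group, two-sided 5% power is 82.5% (84.0% by the normal approximation), against 90% stated. The shortfall for 90% is 33 − 26 = 7 completers per group (6 by the normal approximation), too large to be rounding or choice of formula. Among readings that use only the stated inputs, only a one-sided 5% test yields about 90%, and the article neither declares one nor plans the intervals that would go with it.

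This rests on two assumptions: that the primary test is two-sided, as the 95% intervals indicate, and that the calculation made no use of a baseline correlation, as its wording indicates. If r of about 0.45 or more was in fact assumed, the 90% could be right, but the article would need to say so.

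**What to change.** Keep the enrolment and correct the sentence in the Sample size section. Suggested wording: *With 26 completers per group, an unadjusted two-sided 5% test has about 82% power for a 9.5-point difference in SF-36 MCS (SD 11.6), and 90% power for a difference of about 10.6 points.* It may be added that the planned baseline adjustment is expected to raise power by an amount not quantified.

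Alternatively, if the original calculation did rely on ANCOVA, state the correlation that was used, give its source, and show that 90% follows (about 0.45 or more is required). A value should not be picked now because it reaches 90%.

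Either way, state that the primary test is two-sided at 5%. The cost is one sentence and a less favourable headline power. The design, analysis and number of patients stay as they are.

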### Blinding

After completing the baseline questionnaire and physical fitness tests, the participants will be enrolled and a computer-generated random list generated by SPSS 16.0 will be used for randomization. The random number list is kept strictly confidential by the Data Coordination Committee (DCC) staff. Eligible patients will be randomized to the experimental group or the control group at a 1:1 ratio. The group numbers will be provided in envelopes made from carbonless paper. The envelopes will be kept by a study administrator who will not directly participate in the recruitment or follow-up of any participant and the group numbers will be subsequently disclosed. Different people will enroll participants and assign participants to interventions.

The division results are kept by the study designer until the end of the study to ensure allocation concealment, which means the allocation is bound to both the result evaluator and the data analyzer. The participants and the treatment provider will be instructed not to disclose the allocation to the result evaluator.

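### Enrolling 60 with 15% drop-out leaves 51 expected completers, one short of the 52 the protocol says it needs; dividing by 0.85 gives 62

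*Protocol article*

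**What the plan says.** The Sample size section of the protocol article gives the completer target, the power and the enrolment in two consecutive sentences.

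- The target is a number of completers: "A total of 52 participants (26 in each group) completing follow-up".
- That number "will provide 90% power (α = 0.05) to detect 9.5 points" on the SF-36 mental component summary, "assuming a standard deviation of 11.6 points".
- The step from completers to enrolment is: "Assuming a 15% drop-out rate between baseline and follow-up, 60 participants will be enrolled in the study".

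Three other sections bear on how these figures are read. The Blinding section places randomisation after the baseline questionnaire and fitness tests, and says: "Eligible patients will be randomized to the experimental group or the control group at a 1:1 ratio". The Statistical analyses section plans an ANCOVA adjusted for baseline, on an intention-to-treat population, and leaves missing data out. The Data collection and management section states that there is no plan to promote retention, although clinicians will ask those who quit whether they will still finish follow-up.

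**The concern.** A drop-out rate is a share of those enrolled, so the completer target has to be divided by one minus the rate. Multiplying the target by one plus the rate takes the loss as a share of the completers and always gives too few participants. The printed enrolment looks like the product of the second calculation.

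The completer target, the drop-out rate and the enrolment are given together as the basis for the power claim, and the three cannot all be true. Enrolment is also the number the trial is run to: the Study design section has the data analysed once the sample size is reached. The protocol undertakes to report in line with CONSORT, so an inconsistent sample-size statement would pass into the results paper.

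**Working it through.** **Inputs, from the Sample size section unless noted**

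- Completers required: 52 (26 per group)
- Drop-out between baseline and follow-up: 15%
- Enrolment: 60
- Difference 9.5 points, SD 11.6 points, alpha 0.05; one- or two-sided is not stated
- Allocation 1:1 (Blinding section)
- Missing outcomes left out of the analysis (Statistical analyses section), so each drop-out reduces the analysed number

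**1. Reproducing the printed 60**

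n × (1 + d) = 52 × 1.15 = 59.8, which rounds up to 60. This matches the printed figure.

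**2. The inflation that keeps 52 completers**

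n / (1 − d) = 52 / 0.85 = 61.2. Per arm, 26 / 0.85 = 30.6, so 31 per arm and 62 in total. Check: 62 × 0.85 = 52.7 expected completers.

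**3. What 60 enrolled delivers**

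- Expected completers at 15% drop-out: 60 × 0.85 = 51.0, which is 1 below 52.
- Highest drop-out that still leaves 52: 1 − 52/60 = 13.3%.

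**4. Chance of missing the total of 52**

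Assuming that each participant drops out independently with probability 15%:

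- 60 enrolled: P(Bin(60, 0.85) ≤ 51) = 0.555
- 62 enrolled: P(Bin(62, 0.85) ≤ 51) = 0.323

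**5. Power cost of this slip alone**

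Two-sample t-test with difference 9.5 and SD 11.6, without baseline adjustment:

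| Completers | One-sided 0.05 | Two-sided 0.05 |
|---|---|---|
| 52 (26 + 26) | 89.8% | 82.5% |
| 51 (26 + 25) | 89.2% | 81.8% |
| Loss | about 0.5 points | about 0.8 points |

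The two-sided column lies well below 90% for a separate reason: with these inputs, 26 per arm gives about 90% power only for a one-sided test. Going from 52 to 51 completers accounts only for the last row.

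**The case against.** The arithmetic itself is hard to dispute. The 52 is expressly a count of completers, the 15% is a loss after baseline, and the analysis does not recover those who are lost. The case on the other side concerns how much this matters and what should replace the figure.

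- *The effect is trivial.* One completer and 0.5 to 0.8 points of power would not change how the trial is read. This stands, and the point should be presented as an arithmetic slip.
- *The planned ANCOVA may absorb it.* The documents give no correlation between baseline and outcome, so any value is an assumption. At 0.15, power with 51 completers is already back at the 52-completer t-test level (about 89.8% one-sided, 82.6% two-sided); at 0.3 it is about 91.6% and 85.2%. The loss may therefore have no practical effect. That does not make 60, 15% and 52 agree.
- *62 is right only if 52 is right.* This stands. If the test is two-sided and the power is to be 90% without credit for baseline adjustment, the completer target becomes 64 to 66, and division by 0.85 gives 76 to 78 enrolled.
- *The miss probabilities can mislead.* Even 62 enrolled falls short of 52 about one time in three. If 26 completers are required in each arm, the chance of a miss is about 72% with 30 per arm and 53% with 31. This is fair: inflation secures the target on average and does not guarantee it.
- *The mechanism is inferred.* The protocol shows no formula, and 61.2 could have been rounded down to a convenient 60. That is possible, but the contradiction does not depend on how 60 was reached.

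**Conclusion.** The sample-size statement is wrong as written. Under the protocol's own 15% drop-out, 60 enrolled are expected to give 51 completers, not 52. The enrolment consistent with 52 and 15% is 62 (31 per arm), and the drop-out consistent with 60 and 52 is 13.3%.

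The size is one expected completer, two enrolled participants and less than one point of power. If drop-outs are independent at 15%, the trial is slightly more likely than not (56%) to finish below its stated total.

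The conclusion rests only on the printed figures and on reading drop-out as a share of those enrolled, which the wording and the order of baseline, randomisation and follow-up support. The figure of 62 also takes the 52 as given. The power figures assume an unadjusted t-test.

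**What to change.** Restate the enrolment sentence in one of two ways:

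- 60 participants will be enrolled; 51 are expected to complete at 15% drop-out, with power quoted for 51 and the sidedness of the test stated; or
- 60 participants will be enrolled, which allows for about 13% drop-out while retaining 52.

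Either costs one sentence and leaves recruitment unchanged.

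If the sponsor prefers to keep both 15% and 52 completers, the enrolment must read 62 (31 per arm). That means two more participants and, because recruitment was already under way with ethics approval, whatever amendment a changed target requires. Should the completer target itself be revised, the new figure should be divided by 0.85, not multiplied by 1.15.

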### Data collection and management

To ensure the accuracy of outcome assessments and data collection, all of the physicians, nurses, and research assistants will attend a training workshop before the start of the trial. All attendees will be provided with a protocol and standard operation procedures and will discuss the topics they may feel confused about until everyone is totally clear about the procedures. We do not have plans to promote participant retention and complete follow-up.

After screening and signing of informed consent and end-of-study measurements, the SF-36, physical fitness, and social cognitive theory will be carefully recorded. Monitoring will be performed by personnel independent of the investigators and the sponsor and will consist of checking all informed consent forms and completeness of all data and source data verification of patients. Data are collected and recorded on a standard report form; when the visit is completed, all the recorded data will be entered into the web-based data system by the double-entry method. All errors will need to be corrected by crossing out, with the researcher’s signature and date. Any participant may quit the study at any time for any reason. If any patients want to quit, clinicians will ask whether they agree to finish the follow-up according to the study schedule. All patients who quit and are lost to follow-up will be recorded. If our study fails to recruit 50% of patients within six months, we will stop the study. The process will be independent from investigators and the sponsor.

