### Exclusion criteria

Individuals who meet any of the following criteria will be excluded: (1) those with communication or language barriers and inability to complete the questionnaire; (2) those with metastasis, severe deterioration of conditions, or severe mental disorders; (3) those with a history of acute attempted suicide; (4) those with cognitive organic brain lesions and dementia; (5) those who cannot perform exercises of medium exertion and above; and (6) those who cannot use independently or with help social media app (WeChat official account), free-of-charge commercial smartphone apps, and remote video. Patients who meet one or more of the above criteria will be excluded from the study.

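### The protocol disclaims any retention plan while containing one limited retention step, although its sample size has no margin for extra loss and its analysis disregards missing scores

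*Protocol article*

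**What the plan says.** All references are to the protocol article.

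- **Data collection and management** declares: "We do not have plans to promote participant retention and complete follow-up". A few sentences later it provides: "If any patients want to quit, clinicians will ask whether they agree to finish the follow-up according to the study schedule". For the rest, it says: "All patients who quit and are lost to follow-up will be recorded". No tracing or reminder step is described.
- **Measurements** makes the SF-36 mental component summary the primary outcome and fixes how data are taken: "Measurements will be conducted in the same place and by the same tester for both the study group and control group". No fallback is given for someone who cannot attend.
- **Quality of life (QOL)** describes the instrument: "SF-36 is a reliable and manageable questionnaire of QOL".
- **Exclusion criteria** rule out "those who cannot use independently or with help social media app (WeChat official account), free-of-charge commercial smartphone apps, and remote video". Everyone randomized, in either arm, can therefore be reached by these means, some of them only with a helper.
- **Intervention group** describes roll calls at video sessions, endurance sessions and weekly meetings, for the stated purpose of adherence. **Control group** describes usual care and health education, and no roll calls.
- **Sample size** requires 52 completers (26 per group), assumes 15% drop-out and enrols 60.
- **Statistical analyses** specifies ANCOVA with treatment and baseline, labels the population intention-to-treat and disregards missing data.

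**The concern.** This is a stated decision, not something an article has left to a fuller document. It is a poor decision on the protocol's own terms, for three reasons.

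First, the section disclaims retention measures and then prescribes one. Site staff could read it either way: keep pursuing the outcome, or let people go.

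Second, the one step described depends on the patient announcing that she wants to leave. A patient who does not come to the final assessment is only logged.

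Third, nothing later in the plan makes up for the loss. The completer target has no reserve at the assumed drop-out rate, and the analysis uses only observed scores. Avoidable loss therefore costs power. If it is unequal between arms and related to mental health, it also biases the comparison.

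**Working it through.** **1. The plan's own figures.** Inputs from Sample size: difference 9.5, SD 11.6, α = 0.05 (sidedness not stated), power 90%.

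Per group, n = 2 × (z for α + z for power)² × (SD/difference)², with (11.6/9.5)² = 1.491.

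- One-sided: 2 × (1.645 + 1.282)² × 1.491 = 25.5, so 26. This matches the stated 26.
- Two-sided: 2 × (1.960 + 1.282)² × 1.491 = 31.3, so 32.

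The stated enrolment matches 52 × 1.15 = 59.8, so 60; dividing by 0.85 would give 61.2, so 62. Sidedness and the inflation method are separate issues. They matter here only because they show how little slack there is.

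**2. Completers at the planned loss.** 60 × 0.15 = 9 lost; 60 − 9 = 51, one below 52.

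**3. Power if loss exceeds the plan.** Two-sided normal power ≈ Φ(9.5 / (11.6 × √(2/n)) − 1.960), with n completers per arm. The one-sided column uses the noncentral t distribution. Loss rates above 15% are assumptions.

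| Loss | Completers | Two-sided (normal) | One-sided (t) |
|---|---|---|---|
| 15% | 51 | 83% | 89% |
| 20% | 48 | 81% | 87% |
| 25% | 45 | 78% | 86% |
| 30% | 42 | 76% | 83% |
| 40% | 36 | 69% | 78% |

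These figures take no credit for baseline adjustment.

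**4. What recovery could return.** How many of the nine could be recovered is an assumption. Recovering none leaves 51 completers and 83% two-sided power. Recovering five gives 51 + 5 = 56, above the target: 9.5 / (11.6 × √(2/28)) = 3.064, less 1.960 = 1.104, and Φ(1.104) is about 86.5%. Recovering all nine gives 60 and about 89%.

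**5. Bias illustration.** Suppose a fraction p of an arm is lost and those lost score k points below that arm's completers. The full-arm mean is then the completers' mean minus p × k. The completers-only difference between arms is off by (p₁ − p₂) × k.

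- Equal loss, 15% and 15%, k = 5: (0.15 − 0.15) × 5 = 0.
- 25% and 5% (average 15%, as planned), k = 5: 0.20 × 5 = 1.0 point.
- The same losses, k = 9.5: 0.20 × 9.5 = 1.9 points.

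The arm with more loss looks better than it should. The documents give neither the split nor k; both are assumed. The shift is unadjusted, and ANCOVA would remove whatever part the baseline score explains.

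**6. Whether the fallback fits the rest of the text.** The primary outcome is a questionnaire score, and the eligibility rule secures app and video access in both arms. The rule in Measurements on place and tester does not allow for remote completion, so that sentence must change too.

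**The case against.** The strongest defence has four parts.

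**The protocol does take some steps.** A reader might infer from the disclaimer that nothing at all is done. The documents do not support that: patients who want to leave are asked about finishing follow-up, losses are recorded, and independent monitoring checks data completeness. What stands is narrower. The disclaimer contradicts the question put to quitters, and neither logging nor monitoring recovers a silent loss.

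**Controls are not shown to be out of contact.** A reader might infer that the control arm hears nothing until the final test. The Control group section provides normal treatment, examination and health education. Ethical approval and dissemination mentions assessors who contact participants, without restricting this to one arm. The schedule in Fig. 2 is not available here. All that can be said is that roll calls are described for one arm only, and for adherence. Differential loss is possible but not documented. Its direction is open: contact might hold the exercise arm, or exercise burden might thin it.

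**Drop-out is already budgeted.** Planning for 15% loss without a retention programme is coherent, and 51 rather than 52 completers costs under one point of power (84% to 83%, two-sided normal). This is right as far as it goes. The budget covers the planned rate and nothing above it, and it does not address bias.

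**Remote collection is a suggestion, not an error in the plan.** This is correct. It departs from the same-place rule, some participants may need help to complete a self-report measure, and those who respond remotely may resemble completers more than those still missing. No particular reduction in bias can therefore be promised.

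**Conclusion.** The point holds as an inexpensive improvement to a stated decision; it is not a fatal flaw. The sentence disclaiming retention conflicts with the question put to quitters and leaves silent losses unaddressed. The trial ends at 51 completers against 52 even if drop-out is exactly as planned, and unobserved scores drop out of the analysis.

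The size depends on assumptions. If loss rose to 20–30%, two-sided power would fall from 83% to 81–76%. If loss were 25% in one arm and 5% in the other, with dropouts 5 to 9.5 points lower, the unadjusted completers-only difference would shift by about 1.0 to 1.9 points, which is 11% to 20% of the 9.5-point target (1.0/9.5 and 1.9/9.5). With equal loss and the same dropout deficit in both arms, there would be no such shift.

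**What to change.** In Data collection and management, replace the disclaimer with wording such as:

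> Both arms receive the same scheduled reminders before the 12-week assessment. Participants who stop the intervention are asked to remain in follow-up unless they withdraw consent. Anyone who cannot attend is offered remote completion of the SF-36 and PROMIS, with mode of completion and any help received recorded.

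In Measurements, add a matching exception to the rule on place and tester, and keep in-person assessment as the default. The right to withdraw freely, set out under Participants and recruitment, is unaffected.

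The cost is small: reminders and a remote questionnaire, using channels that eligibility already requires participants to be able to use. The downsides are that a few scores come from a different mode, sometimes with a helper present, and that the ethics committee must be notified. Trial status reports recruitment as still under way at submission, so the change could still have been made at that stage.
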